### **8.4. Recording and assessing AEs and SAEs**

AEs will be recorded within the case report form and entered onto the study website. All relevant information should be captured on the case report form. The information should be entered onto the study website within 72 hours (3 days) of the event being identified.

The Principal Investigator (or delegate) for each site will review the AEs and make an evaluation of seriousness, causality and expectedness and record this within the case report form. The evaluation of AEs should be done and entered onto the study website within 7 days of the event being identified by the field worker.

#### **Assessment of Seriousness**

An assessment of seriousness, as defined in Table 2 above will be made.

#### **Assessment of Causality (relatedness)**

- Related: resulted from administration of any of the research procedures or to the man's effort to lose weight
- Unrelated: where an event is not considered to be related to any of the research procedures or to the man's effort to lose weight.

Alternative causes such as natural history of the underlying disease (obesity; co-morbidities), concomitant therapy, other risk factors and the temporal relationship of the event to the treatment will be considered.

## Assessment of Expectedness

If the event has been assessed as being related to the administration of any of the research procedures or to the man's effort to lose weight, an assessment of expectedness is required. The following events are expected:

- Musculoskeletal injuries or musculoskeletal pain
- Cardiovascular events (such as angina, myocardial infarction, palpitations, etc)
- Nutritional deficiencies
- Gall stones, newly manifest or worsening of known symptoms
- Changes in bowel habits
- Negative impacts on mental health (such as depression, fatigue, suicidal thoughts, etc)
- Low blood sugar, changes in diabetic medication, diabetic complications

All other events are considered unexpected.

## 8.5. Review of AEs and SAEs

The Chief Investigator or medically qualified delegate will review the following categories of AE within 72 hours (3 days) of the PI assessment:

- Serious adverse events that have been assessed by PI as related and not expected. *{These SAEs require to be reported to the REC and should have medical oversight and input as the report is prepared}*
- Serious adverse events that have been assessed by PI as not related. *(We recommend medical oversight on these events to confirm that they are not related)*

Serious adverse events that have been assessed by the PI as related and expected will be collated and reviewed by the PMG and TSC at their meetings – they do not need real-time review by the CI or medically qualified delegate. Likewise, non-serious adverse events will be collated and reviewed by the PMG and TSC at their meetings. The PMG and TSC will be blind to treatment allocation when reviewing SAEs and AEs. The independent TSC will also have the role of a Data Monitoring Committee to provide oversight of safety within the trial.

## 8.6. Reporting AEs and SAEs to REC

If, in the opinion of both the PIs and the CI, the event is confirmed as being serious and related and unexpected, the CI or Trial Manager will notify the Sponsor within 24 hours of the CI (or medically qualified delegate) confirmation. The Sponsor will provide an assessment of the SAE. A Sponsor cannot downgrade an assessment from the PI or CI. Any disparity will be resolved by further discussion between these parties. The CI or delegate will report any related and unexpected SAEs to the REC within 15 days of the event being identified.

If all the required information is not available at the time of reporting, the Fieldworker must ensure that any missing information is provided as soon as this becomes available. It should be indicated on the report that this information is follow-up information of a previously reported event.

All related SAEs will be summarised and reported to the Research Ethics Committee, the Funder and the Trial Steering Committee in their regular progress reports.

## 8.7. Responsibilities

**Table 3. Responsibilities for collecting data on adverse events**

|                                      |                                                                                                                                                                                                                                                                           |
|--------------------------------------|---------------------------------------------------------------------------------------------------------------------------------------------------------------------------------------------------------------------------------------------------------------------------|
| Fieldworkers                         | 
 
• Ask about the occurrence of AEs/SAEs
 
• Record information about AEs on the CRF and enter this information onto the study website within 72 hours (3 days) of the event being identified*
 
                     |
| PI or delegate                       | 
 
• Review and assess AEs, and ensure this information is recorded on the study website within 7 days of the event being identified
 
                                                                                       |
| Trial managers                       | 
 
• Ensure that relevant SAEs are reviewed by the CI (or medically qualified delegate)
 
• Report SAEs that are related and unexpected to REC
 
• Collate summaries of AE and SAEs for PMG and TSC meetings
 
 |
| CI (or medically qualified delegate) | 
 
• Review relevant SAEs within 72 hours (3 days) of the PI assessment
 
                                                                                                                                                    |

\* Any member of the research team have this responsibility if they are the first to receive information about an AE.

## 8.8. Safeguarding

In the text message intervention groups, men may reply to the text messages being delivered. The Health Informatics Centre in Dundee have experience of automatically screening incoming text messages from participants in similar studies[31-33] for words like 'suicide', 'die', 'death', 'help'. The trial will use this screening process.

In the intervention groups, if a text message from a participant contains a keyword (e.g. help, suicide, death, die) the message is given high importance. Monitoring will run for the duration of the trial assessment period (24M). The HIC monitoring service will send the message in an email to appropriate researchers (the site Fieldworkers and the Trial Managers), providing the participant ID number and content of the text message.

If the research team is concerned regarding the content of a message, they will discuss this with a senior colleague (CI or medically qualified delegate). Similarly, if any issues are raised during any contact with a participant that cause concern (for example if a participant tells a Fieldworker that he feels suicidal), this will be discussed with the PI, and then CI or medically qualified delegate. In these circumstances, the allocation can be unblinded if necessary, and a course of action will be agreed. If the safety of the participant or of another person was thought to be at risk, a member of the research team will alert appropriate services: informed consent is sought for this when men join the study.

Patient information leaflets and information available on the GoS website will provide local and national contacts where men can access support.

## **9. STATISTICS AND DATA ANALYSIS**

A Statistical Analysis Plan (SAP) will be produced separately by the trial statisticians. A separate SAP will be prepared for the 24M outcome data after TSC approval to proceed to 24M data collection.

### **9.1. Sample size calculation**

We will require to follow up 146 men in each group to detect differences in weight loss between groups of at least 3% at 12M, with 90% power and two-sided alpha equal to 2.5% (to maintain a nominal significance level of 5% with two tests being used). With an expected 25% loss to follow-up as observed in the Feasibility Study at one year, a total of 585 men will need to be randomised: 195 per trial group and 195 (65 per trial group) at each of the three centres.

The sample size calculation is based on detecting a mean difference in weight between intervention groups and control of at least 3.3kg, assuming a pooled standard deviation of 8kg. A minimum clinically important weight loss of 3% is recommended by NICE [9], and the mean difference of 3.3kg is derived from 3% of 109kg (the mean baseline weight in the Feasibility Study). Several trials of SMS-delivered weight management interventions [12] reported an effect size >3.3kg, including the largest study which was the only trial to include predominantly men, suggesting 3.3kg is an achievable mean weight loss. The standard deviation for absolute weight loss ranged from 4.9kg to 6.3kg in the Feasibility Study (at 12M) and from 2.5kg to 7.3kg in the systematic review. We therefore conservatively assume a standard deviation of 8kg.

### **9.2. Planned recruitment rate**

The estimated randomisation rate for men recruited is 25/centre/month over 8 months. This is based on Feasibility Study data: Community recruitment took on average 2.3 recruiter hours per participant randomised and GP letters had an opt-in rate of 10.2% (n=90/879). Recruitment will be flexible, including at weekends and in the evenings, enabling men who work to join the study. There are three recruiting centres covering very wide urban, suburban and more rural areas which will provide diversity and many potential venues for recruitment. GP Practices will range in the size/percentage of the population meeting eligibility criteria, and the expected consent rate.

In our Feasibility Study we proposed to use adverts via local newspapers, circulars and social media in collaboration with local community stakeholders, if recruitment rates were lower than anticipated. They were not required as more men expressed interest in joining than could be accommodated. These remain in the current protocol, as they are more Covid-19 resilient recruitment methods than manned stands in community venues.

### **9.3. Statistical analysis plan**

A single analysis will be conducted once primary outcome data collection is complete, following a pre-specified Statistical Analysis Plan developed according to recently published guidelines [52]. The

analysis will be undertaken blind to group allocation by a statistician at CHaRT who will not have access to the HIC verified weight data at 3 and 6M which are part of the intervention. The HIC dataset for subsequent analyses, will be provided after the primary analysis has been completed. This solves the blinding issue in our Feasibility Study [2] due to different group assessment schedules (3 and 6M assessments for the intervention groups only).

All outcome measures will be summarised with the appropriate descriptive statistics where relevant: mean and within-participant change in weight from baseline to 12 months expressed as a percentage of baseline weight, mean and standard deviation for continuous outcomes (or medians and interquartile range for skewed data) and counts and percentages for dichotomous and categorical outcomes.

The primary analysis will follow CONSORT reporting guidance and will be by intention to treat using multiple imputation of missing outcome data. Analysis to account for non-compliance is not necessary, as automated interventions can only be accessed via randomisation, therefore cross-over cannot occur and contamination was minimal in the Feasibility Study. This is a self-management intervention, therefore stopping the text messages but continuing to attend weight assessments is compliant.

Exploratory sub-group analyses are hypothesis generating to inform future research and implementation and will be reported separately after the primary outcome analysis is complete.

### **9.3.1 Summary of baseline data and flow of patients**

The variables used to describe our sample are consistent with those reported in the Feasibility Study [1]: age, weight, height, BMI, deprivation category, partnership status, co-morbidities, ethnic group, education, working status, household size, weight loss history and strategies used, physical activity and sedentary behaviour, alcohol frequency, smoking status, confidence in ability to lose weight and to maintain weight loss, EQ-5D-5L and the Warwick-Edinburgh mental well-being scale (WEMWBS). Definitions and rules for derivation of these measures were set out in the statistical analysis plan for the Feasibility Study and will be incorporated into the SAP for the full trial. New variables include disability and access to self-monitoring equipment (scales, activity tracker). “Perceived wealth”[23] and “Financial Strain”[24, 25] are included to capture additional health inequalities data. Baseline data for the additional exploratory research for men living with obesity and mental health conditions and/or MLTC are: MLTC with or without diabetes.

A CONSORT flow diagram will be produced similar to the report of the Feasibility Study [1].

### **9.3.2 Primary outcome analysis**

The analysis of the primary outcome will estimate the mean difference in change from baseline weight expressed as a percentage at 12M between groups (SMS+I vs control; and SMS only vs control),

using a linear regression model adjusting for minimisation variables, with recruitment centre as a fixed effect.

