Pedometers are given to all participating men in Game of Stones to encourage self-monitoring. All men (including wait-list arm) will have access to a Game of Stones website which includes links to evidence-based information about weight loss, and to charities like Men's Health Forum which support men's physical and mental health.

This trial will recruit from diverse areas in three UK countries to provide generalisable evidence on effectiveness, cost-effectiveness and impact on health inequalities relevant for policy makers and service commissioners. Programming for transferability will involve public service technology experts so that SMS and incentives can in future be delivered centrally or locally, together or separately. Measuring weight by health care assistant or equivalent staff in health or community venues was feasible [2]. This self-care intervention can accommodate future technological advances in digital scales linked to databases to minimise staff resource requirements. Commissioners tell us that variations in effect sizes

by socio-economic group and levels of co-morbidity will be important to inform how Game of Stones might contribute to current weight management services.

In summary, Game of Stones targets a clear evidence gap in weight management services and health inequalities for men. Obesity, health inequalities and prevention are all UK policy priorities in the NHS Long Term Plan ([www.longtermplan.nhs.uk](http://www.longtermplan.nhs.uk)) and are likely to remain so for the foreseeable future, particularly with new evidence emerging about risk factors for Covid-19. In a female dominated weight management landscape, NHS service commissioners want to know whether financial incentives with text messages can make a difference to improve obesity outcomes for men.

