### **4.2. Primary objective**

To conduct a 3-arm RCT to estimate between group difference in % weight change at 12M from baseline for men with obesity who receive i) SMS+I; ii) SMS only; iii) 12M wait list for SMS

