## **9.9. Economic evaluation**

A full economic evaluation will be conducted. This will include a trial-based analysis and a decision model to assess economic value over an extrapolated lifetime horizon. The primary economic outcome

will be incremental cost per Quality Adjusted Life Year (QALY). A Cost Effectiveness analysis (incremental cost per % weight loss) will also be performed. Firstly, these analyses will be performed using the 12M follow-up data, then updated if the study progresses to Phase 3 (24M follow-up).

**Estimation of costs:** The resources associated with the interventions will be measured using study-specific forms. Other NHS resource-use (GP, nurse, emergency department, outpatient appointments and inpatient stays) will be collected via participant reported questionnaires at baseline, 12 and 24M. The costs of NHS/Public Health funded weight loss services will also be included. Resource use estimates will be combined with unit costs obtained from standard sources or study specific estimates. Incremental costs (NHS perspective) will be estimated using generalised linear models with appropriate distributions for cost data and adjustment for baseline covariates.

**Estimation of benefits:** We will measure benefits in terms of QALYs gained, based on participant responses to the generic EQ-5D-5l health related quality of life measure at baseline, 12 and 24M if the study progresses to Phase 3. Incremental QALYs will be estimated using generalised linear models with adjustment for baseline covariates.

**Trial based economic evaluation:** Costs and benefits will be combined to estimate cost per QALY gained over the 12M follow up period. A full incremental analysis will be performed. A cost per % weight loss will also be estimated. Deterministic sensitivity analyses will be undertaken to test the impact of assumptions and analysis methods on results. Results will be plotted on cost-effectiveness planes to illustrate the impact of sampling uncertainty on results. The analysis will be updated if the study progresses to Phase 3.

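### Section 9.3.2 names only the two contrasts with control, so the effectiveness analysis gives no direct estimate of what the incentive adds to SMS

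*Protocol*

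**What the plan says.** Section 9.3.2 defines the primary analysis as the mean difference in weight change "expressed as a percentage at 12M between groups (SMS+I vs control; and SMS only vs control". The parenthesis reads as a complete list. Section 9.1 agrees with it: the alpha is "two-sided alpha equal to 2.5% (to maintain a nominal significance level of 5% with two tests being used", and the calculation rests on "detecting a mean difference in weight between intervention groups and control of at least 3.3kg", "assuming a pooled standard deviation of 8kg". Section 9.3.3 analyses secondary and exploratory outcomes in a similar way, at the 2.5% level.

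Other sections reach further than the two contrasts with control:

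- Section 4.2, the primary objective, is worded over all three groups: "To conduct a 3-arm RCT to estimate between group difference in % weight change at 12M from baseline".
- Section 7.3.2 is headed as an incentive given as an adjunct to SMS.
- Section 9.9 plans a cost per percentage weight loss and says "A full incremental analysis will be performed".
- Section 3.1 foresees SMS and incentives being delivered jointly or on their own.

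The research question in 4.1 is narrower. It asks about SMS, with or without incentives, against the waiting list.

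**The concern.** Two active arms differ by one component, the incentive, and that component carries the payments. Anyone choosing between the two arms needs the difference between them, with its uncertainty. Section 9.3.2 as written yields two separate comparisons with control. If one is significant and the other is not, readers may conclude that the incentive did or did not help, and a comparison of two significance verdicts cannot support that. A contrast added only after the results are known would also be open to the charge of selective reporting.

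A smaller, separate matter is the multiplicity rule. A fixed 2.5% per test is plain Bonferroni. A step-down rule keeps the same 5% family-wise error and rejects everything that Bonferroni rejects, and sometimes more.

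**Working it through.** **Inputs (section 9.1):** difference 3.3 kg (3% of 109 kg is 3.27 kg), SD 8 kg, two-sided alpha 2.5% per test, power 90%, 25% loss to follow-up, equal allocation. Feasibility Study SDs: "The standard deviation for absolute weight loss ranged from 4.9kg to 6.3kg in the Feasibility Study (at 12M").

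**1. The plan's own figure.** n per arm = 2 × (8/3.3)² × (2.241 + 1.282)² = 2 × 5.877 × 12.41 = 145.9, so 146. Then 146/0.75 = 194.7, so 195 per arm and 585 in total. Both match the protocol.

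**2. Precision of SMS+I minus SMS.** SE = 8 × √(2/146) = 0.936 kg.

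- 95% half-width: 1.96 × 0.936 = 1.84 kg, and 1.84/109 = 1.7 percentage points.
- At SD 6.3 kg, the top of the Feasibility Study range: SE = 6.3 × √(2/146) = 0.737 kg and half-width 1.45 kg, or 1.3 points.

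The conversion to points divides by the 109 kg mean baseline, as 9.1 does.

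**3. What that contrast could detect.** The protocol gives no expected SMS+I minus SMS difference, so these are assumed values, with power at two-sided 5% and 146 per arm:

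| Assumed difference | SD 8 kg | SD 6.3 kg |
|---|---|---|
| 1 kg | 19% | 27% |
| 2 kg | 57% | 77% |
| 3.3 kg | 94% | 99% |

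The contrast is therefore informative as an interval, but weak as a test of a small increment.

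**4. Fixed 2.5% against Holm.** Simulation of three independent arms, 1,000,000 replicates, 146 per arm and SD 8 kg. The shared control gives a correlation of 0.5 between the two contrasts.

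| True effects 3.3 kg in both arms | Fixed 2.5% | Holm at 5% |
|---|---|---|
| Power, each test | 90% | 93% |
| Power, both | 83.3% | 89.4% |
| Power, at least one | 96.8% | 96.8% |

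The last row must be equal, because Holm's first step is the 2.5% test. It also follows from the components: 0.9007 + 0.9002 − 0.8331 = 0.9678 for the fixed rule, and 0.9312 + 0.9304 − 0.8938 = 0.9678 for Holm. With no true effect in either arm, the family-wise error is 4.7% under both rules.

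**5. A smaller SMS effect.** Section 3.1 reports a pooled SMS effect of 2.28 kg. With SMS+I at 3.3 kg and SMS at 2.28 kg, the SMS-only test at 2.5% has z = 2.28/0.936 − 2.241 = 0.19, or power 58%. Holm gives 67%. At SD 6.3 kg the fixed rule alone gives z = 2.28/0.737 − 2.241 = 0.85, or 80%.

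**The case against.** The strongest reply is that the two listed contrasts answer the research question in 4.1, which is framed against the waiting list, and that 9.1 sizes the trial for exactly those two. That stands: 9.3.2 does not contradict 4.1. Nor does the objective in 4.2 promise every pairwise contrast. It merely does not exclude the one between the active arms.

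A reader might infer that the protocol never compares the two active arms. The document does not support that. A full incremental analysis of three options ordinarily sets SMS+I against SMS on costs and effects, so 9.9 implies the comparison. The separate analysis plan, not seen here, may also add it. What remains is that the effectiveness section gives a closed list without this contrast, while the economic section depends on it.

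The statement in 3.1 that "NHS service commissioners want to know whether financial incentives with text messages can make a difference" is weak support, since it can be read as asking about the combined package, which SMS+I against control answers.

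A reader might also infer that the 2.5% rule is a mistake, or that it leaves the trial short of power. It is not a mistake: it controls the error rate and delivers its stated 90%. The progression rule in 2.1 needs success on only one comparison, and for that Holm gains nothing. The fixed rule also keeps each test in step with its 97.5% interval. The 58% figure should not carry weight alone. It pairs a mixed-sex pooled effect, from trials with a median duration of 6 months, with an SD that the protocol calls conservative. Section 9.1 also reports several SMS trials with effects above 3.3 kg.

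**Conclusion.** The point holds in a limited form. The effectiveness analysis names no direct estimate or interval for the incentive's added effect, although the design, the adjunct framing and the economic plan all call for one. It can be had from the existing data to within about ±1.8 kg (1.7 points) at SD 8 kg, or ±1.45 kg at SD 6.3 kg, assuming 146 men per arm with outcome data and equal variances. It would be an estimate, not a powered test.

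The multiplicity point is optional. Holm would add about 3 points of power per test and about 6 points for showing both, if both true effects are 3.3 kg and the SD is 8 kg. It would add none for showing at least one. The stated rule and the sample size of 585 are sound.

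**What to change.** **Main change.** Add to 9.3.2 that SMS+I minus SMS will be estimated from the same model and reported with a 95% confidence interval, as a secondary contrast outside the error-controlled family. State that it is for estimation and that the trial was not sized for small differences between the active arms. Say also that the 2.5% level in 9.3.3 does not apply to it. The cost is one or two sentences in the protocol, matched in the analysis plan. No extra men or data are needed, and the two primary tests are untouched.

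**Optional change.** Replace the fixed 2.5% for the two primary tests with Holm at 5% overall: the smaller p-value is tested at 2.5% and, if it is significant, the other at 5%. Keep the 97.5% intervals for the two contrasts with control, and state that a Holm decision on the second test can differ from its interval. The sample size in 9.1 needs no revision.
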